## Discussion

There is a relevant and growing interest in establishing a consensual and protocolled treatment approach in patients who have presented a FEP. For this reason, the tendency of public mental health network is to form high-risk psychosis and FEP care units (64), employing a multidisciplinary treatment approach including psychiatric, psychological, nursing and social interventions. While the main objective from a medical perspective is focused on alleviating the patients’ psychiatric symptoms, psychosocial approaches mainly aim to support patients and improve their insight and adherence through psychoeducation and disease awareness. The results for specific early interventions in early phase psychosis are more effective than treatment as usual (65), but usually do not include assessment and treatment of the presence of comorbid prior or current psychological trauma. As stated before, patients with psychosis have a high prevalence of psychological trauma during their lifetime which has an important negative impact on the course and prognosis of the disease (3). Beyond the high prevalence of psychological trauma, the diagnosis of a FEP and psychiatric admission represents *per se* a further risk factor of developing another vital traumatic event (15), in this case PPS. Taking this into account, it is important to explore new psychological approaches focusing on psychological trauma to reduce its impact in these patients. More recent psychotherapies, such as EMDR, have achieved increasing popularity and interest from clinicians due to their ability to integrate cognitive, emotional and behavioral components within the same approach. Preliminary evidence suggests that EMDR is as effective and safe as exposure therapy in patients with PTSD and chronic schizophrenia (66, 67) and other severe mental disorders (23, 26). Up to now, to the best of our knowledge, no study has investigated a trauma-focused intervention in FEP patients. The objective of this first trial of this character is to provide further evidence of a positive effect of EMDR in this population in a large RCT, in terms of relapse reduction and improvement in clinical variables. The strength of our study is the inclusion of a 1-year follow-up to test if possible improvements are maintained. With the results from a large RCT, we aim to promote trauma-oriented therapies in patients with a FEP that could be included in specific care units designed to treat this population. Although it has been shown that there is a clear association between PTSD and psychotic disorders, most mental health care programs do not offer trauma-oriented therapies for patients with a FEP so far.

## Limitations

One limitation of this study is the inclusion of both affective and non-affective FEP, as well as comorbid substance use disorders, leading to a more heterogeneous sample. These inclusion criteria were decided on to ensure the study was carried out on a representative real-world population. We suggest this limitation can be addressed by matching the samples in both arms. Additionally, the main underlying clinical variable common to all patients is the presence of comorbid psychological trauma. Another potential source of bias is the lack of control regarding pharmacological treatment. To partly overcome this limitation, a ‘pharmacological treatment’ variable will be included and, to the extent it is possible, patients in the study should not have their drug therapy altered once they are stabilized. As our unit has extensive experience in treating FEP patients and uses standardized treatment protocols, this will also help limit this as a potential source of bias.

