### Randomization Procedure

After the baseline (T0) assessment (see later), we will randomly allocate participants to the EMDR or TAU group following a biased coin procedure (29). We want to note that in small clinical trials, simple randomization may lead to substantial imbalance in the relevant confounding factors between groups. The biased coin procedure attempts to balance these confounding factors but it still randomizes the patients and conceals their allocation (30). It has been included in the international guidelines for drug clinical trials (31) adopted by the European Community, Japan, United States FDA, Canada and Switzerland (32).

Specifically, a computer in a central location will allocate the patients as follows: (a) it will randomly allocate the first two patients to one group or the other with p = 0.5, (b) it will allocate the next patients as follows: (b1) if one group already includes at least two more patients than the other group, it will randomly allocate the patient allocated to the smallest group with p = 0.8, (b2) otherwise, it will first simulate that the patient is allocated to EMDR and calculate the sum of the between-group square standardized differences in age, sex and years of education, it will then simulate that the patient is allocated to TAU and recalculate the sum, and finally it will randomly allocate the patient to the group associated to the smallest sum with p = 0.8. Following this procedure, the final groups should be balanced in size and matched in age, sex and years of education. An independent researcher in a central location will control the computer program that will carry all steps of the randomization process.

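### Matching is offered as the remedy for mixed diagnoses and substance use, but the allocation algorithm matches only on arm size, age, sex and years of education

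*Protocol article*

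**What the plan says.** Under Limitations, the protocol article points to the "inclusion of both affective and non-affective FEP, as well as comorbid substance use disorders, leading to a more heterogeneous sample". The remedy it gives is matching: "We suggest this limitation can be addressed by matching the samples in both arms". It adds that all patients share comorbid psychological trauma. For a second limitation, uncontrolled medication, it promises a dedicated variable. It promises none for diagnosis or substance use.

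Randomization Procedure justifies a biased coin because "in small clinical trials, simple randomization may lead to substantial imbalance in the relevant confounding factors between groups". It then sets out the algorithm in full. Unless the arms already differ in size by two or more, the program has to "calculate the sum of the between-group square standardized differences in age, sex and years of education" under each possible assignment and favour the arm with the smaller sum. The result claimed is that "the final groups should be balanced in size and matched in age, sex and years of education".

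The Statistical Analysis section names neither diagnosis nor substance use as a covariate. It allows variables found significant to enter a logistic or linear regression on effect magnitude and predictors of functioning.

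**The concern.** A reader of the Limitations section would take it that the arms are matched on affective versus non-affective diagnosis and on substance use. The algorithm does not do this: neither factor is in the balancing sum, and no stratification is described. The article thus leaves to chance the two factors it singles out as making the sample heterogeneous, after giving chance imbalance in a small trial as its reason for not using simple randomization.

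If diagnosis or substance use predicts relapse, a chance imbalance shifts the observed relapse difference in that particular trial. An unadjusted analysis also loses some precision. With 40 patients per arm, moderate imbalances are not rare.

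**Working it through.** **The sections side by side.** Factors named as the problem (Limitations): affective/non-affective diagnosis; substance use disorder. Factors balanced (Randomization Procedure): arm size; age; sex; years of education. The two lists have no item in common. The algorithm is given with every step, probability and variable, so this is not a detail lost when the protocol was condensed into an article.

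**Whether the factors are available in time.** Allocation follows the T0 assessment. The qualifying diagnosis is an entry condition (Participants). Substance use is listed at enrolment in Table 1 and at T0 in Table 3. Both are known before allocation.

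**Size of the risk.** The article gives no figure for imbalance in these factors, so there is none to reproduce.

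Inputs from the article:
- 80 patients, 40 per arm.
- The first two patients are allocated with p = 0.5.
- Then 0.8 to the smaller arm "if one group already includes at least two more patients than the other group".
- Otherwise, "randomly allocate the patient to the group associated to the smallest sum with p = 0.8".

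Assumptions, not from the article:
- Affective share of 20% to 50%.
- Substance use disorder in 40%.
- Half of patients female.
- Diagnosis and substance use independent of age, sex and education.

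*Approximation.* For a factor outside the sum with prevalence p, the between-arm difference has standard error √[2p(1−p)/40].
- p = 0.2: √(2 × 0.16/40) = 0.089; 0.15/0.089 = 1.68; two-sided tail about 9%.
- p = 0.3: √(2 × 0.21/40) = 0.102; 0.15/0.102 = 1.46; about 14%.
- p = 0.4: √(2 × 0.24/40) = 0.110; 0.15/0.110 = 1.37; about 17%.
- p = 0.5: √(2 × 0.25/40) = 0.112; 0.15/0.112 = 1.34; about 18%.

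*Simulation of the stated rule* (1,200 trials or more per scenario):

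| Affective share | Gap ≥ 15 points, rule as stated | Gap ≥ 15 points, both factors in the sum |
|---|---|---|
| 20% | 9–10% | 0.5% or less |
| 30% | 14% | 0.5% or less |
| 40% | 17–18% | 0.5% or less |
| 50% | 18% | 0.5% or less |

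Monte Carlo standard error at 18% with 1,200 trials: √(0.18 × 0.82/1200) = 0.011, about one percentage point.

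For comparison, sex, which is in the sum, differs by at least 10 points in about 2% of trials under the stated rule. Diagnosis does so in 27% (20% affective) to 41% (50% affective). With both factors added, the figure for diagnosis falls to about 3% to 5%, and that for sex rises to about 4% to 5%.

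**Effect on the relapse comparison.** This step needs a further assumption, that relapse risk is 50% in one diagnostic group and 25% in the other.
- Gap of 15 to 20 points: 0.15 × 0.25 = 0.038 to 0.20 × 0.25 = 0.050, or 4 to 5 points of relapse.
- Median gap at 40% affective, 7.5 points: 0.075 × 0.25 = 0.019, or 1.9 points.
- Overall relapse is 0.4 × 0.50 + 0.6 × 0.25 = 35% or 0.4 × 0.25 + 0.6 × 0.50 = 40%, depending on which group has the higher risk. The standard error of the risk difference is √(2 × 0.35 × 0.65/40) = 0.107 to √(2 × 0.40 × 0.60/40) = 0.110.
- Even 5 points is under half a standard error: 0.050/0.107 = 0.47.

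**The case against.** The best defence is that allocation is still random. Both factors are balanced in expectation, and chance imbalance is already covered by the error rate of the test. This stands. With no treatment effect and the assumed 50% versus 25% relapse risks, simulation of the stated rule gave unadjusted rejection rates of 0.4% to 0.5% at the article's alpha of 0.005, and 5% to 6% at 0.05. A reader might infer that the relapse comparison is confounded; the documents do not support that.

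The Limitations sentence is also a suggestion, and shared trauma is offered beside it. To say that the design depends on this matching would go too far. The suggestion is still the main remedy given, and it does not fit the algorithm.

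Covariates for the primary model are often fixed in a statistical analysis plan, which is not shown here. So it cannot be said that no analysis will adjust for these factors, only that the article names no such adjustment. The point rests on the disagreement between two sections, not on that absence.

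A reader might want to add centre, since four sites take part. The article neither names centre as a source of this heterogeneity nor claims to match on it, so there is no inconsistency to correct.

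Finally, even perfect matching would only equalize the arms. It would not remove heterogeneity within the sample or any difference in treatment effect between diagnostic groups.

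**Conclusion.** The point holds as an internal inconsistency with a modest practical consequence. Matching is put forward for diagnosis and substance use, while the fully specified algorithm matches on arm size, age, sex and years of education. What is at stake is chance imbalance and lost precision, not bias or an inflated error rate.

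The size depends on an affective share the article does not give: at 20% to 40%, about 10% to 18% of trials would show a gap of at least 15 points, a risk that is almost entirely avoidable. The 4 to 5 points of relapse apply only in that tail and only under the assumed relapse risks, so they should not be read as an expected error. The mismatch between the two sections depends on none of these assumptions. It is worth correcting because the correction is cheap.

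**What to change.** For patients still to be allocated, add affective/non-affective diagnosis and substance use disorder (yes/no) to the sum of squared standardized differences in step b2. As binary variables they can be handled in the same way as sex. Prespecify both as covariates in the primary relapse analysis, whichever model is used; the article names Cox regression only in its sample size section.

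If allocation is complete or the algorithm cannot be changed, make only the analysis adjustment, and correct the Limitations sentence to say that covariate matching covers age, sex and years of education only.

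Costs: a protocol amendment across four centres and their ethics committees; a change to the central allocation program; very slightly weaker balance on the existing factors (for sex, a gap of at least 10 points in about 4% to 5% of trials instead of 2%); and one degree of freedom per covariate, two in all. No new data are needed.

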## Ethics Statement

The study has been approved by the Ethics Committee of the IMIM, Parc de Salut Mar (2018/7940/I), by the Vic Hospital (AC 269), Hospital Mutua of Terrassa, and Althaia Xarxa Assistencial Universitària of Manresa (CEI 19/62).

